#### *11.8.1.3 PBMC analysis*

Following centrifugation of the venous blood samples collected pre-dose on Day 1 and pre-dose on Day 19, and after removal of the plasma, the remaining fraction should be mixed with 2 mL 30% glycerol and frozen at -70°C.

#### **11.8.2 *Biopsy for analysis of local exposure of CXCL12 in the wound, immunohistochemistry, and histopathology (SAD part only)***

On Day 1, one biopsy per subject generated during the wound incision process (Section 11.4) will be saved for baseline histology analysis. In addition, on Day 3, approximately 48 hours after dose, punch biopsies (8 mm) from one wound per arm will be sampled under local anesthesia (injected and/or topical). Following biopsies, compression for hemostasis will be applied if necessary. The residual 2 biopsy wounds will be closed using 1-2 surgical sutures (Prolene®, polypropylene) and dressed as appropriate. The other 2 wounds will be left untouched for continued analysis. For removal of the sutures, subjects may be referred to a local district health care center.

Half the biopsy sample will be snap frozen on dry ice, half will be fixed in 4% formalin.

Details on the procedure will be specified in a separate manual.

The data will be delivered in external files.

#### **11.8.3 *Assessment of wound healing and wound rupture***

The Investigator and the independent evaluators will assess the wound healing status of each wound by direct inspection or by evaluation of photographs, respectively, at visits specified in Table 8.1-1 and Table 8.1-2.

Wound healing, i.e. complete wound closure, is defined as skin re-epithelialization without dressing requirements.

The results of the assessment will be reported in the eCRF as “Yes” or “No” per wound. At each post-wound healing visit, it should be documented if the wound is still healed or if any rupture(s) has occurred.

#### 11.8.4 *Wound area measurements*

The independent evaluators will perform wound area measurements of each wound based on photographs using the Image J software (National Institutes of Health [NIH]) or equivalent at visits specified in (Table 8.1-1 and Table 8.1-2).

#### 11.8.5 *Evaluation of scar tissue formation*

An overall assessment of scar formation (normal/abnormal per wound) will be performed by the Investigator and by independent evaluators at visits specified in Table 8.1-1 and Table 8.1-2. The outcome will be documented per wound/scar in the eCRF.

##### 11.8.5.1 *Vancouver scar scale*

The Burn Scar Index, or Vancouver Scar Scale, is widely used in clinical practice and research to document change in scar appearance over time. The scale scores the scar on four parameters: pigmentation, vascularity, pliability and height. Each scar will be evaluated by the Investigator and by independent evaluators as detailed in Table 11.8-1

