|                                                                                                   | Reduction in wound area and granulation area measurements                             | SAD+ MAD | Independent evaluators (photography)                                               | Wound area measurements (Section 11.8.4)                     |
| To assess the occurrence of wound rupture                                                         | Frequency of wound ruptures                                                           | SAD+ MAD | Investigator (direct observation)

Independent evaluators (photography)      | Wound rupture assessment (Section 11.8.3)                    |
| To assess scar tissue formation                                                                   | Overall scar tissue formation (normal/abnormal)                                       | SAD+ MAD | Investigator (direct observation)

Independent evaluators (photography)      | Overall assessment of scar tissue formation (Section 11.8.5) |
|                                                                                                   | Vancouver Scar Scale total score on Day 21 and onwards                                | SAD+ MAD | Investigator (direct observation)

Independent evaluators (photography)      | Vancouver scar scale (Section 11.8.5.1)                      |

| Objective                                                                                                                                      | Endpoint                                                                                             | Part        | Evaluator | Assessment(s)                                                                                                                                                                                                                      |
|------------------------------------------------------------------------------------------------------------------------------------------------|------------------------------------------------------------------------------------------------------|-------------|-----------|------------------------------------------------------------------------------------------------------------------------------------------------------------------------------------------------------------------------------------|

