| Wound healing                                  |                 |                           |                 | X               | X               | X                                   |                     |                   |                  |                   |                      |                  |        |
| Wound area                                     |                 | X            | X               | X               | X               | X                                   |                     |                   |                  |                   |                      |                  |        |
| Scar tissue formation                          |                 |                           |                 |                 |                 | X                                   | X                   | X                 | X                | X                 | X                    | X                |        |
| Skin swab for analysis of L. reuteri colonies        |                 |                           |                 | X               |                 | X                                   | X                   |                   |                  | X                 | X                    | X                |        |
| Hand out of feces sampling kit                              | X               |                           |                 |                 | X               | X                                   |                     |                   | X                | X                 | X                    | X                |        |
| Feces sample for analysis of L. reuteri colonies     |                 | X             |                 |                 |                 | X                                   | X                   |                   |                  | X                 | X                    | X                |        |
| Dressing                                                    |                 | X                         | X               | X               | X               | X                      |                     |                   |                  |                   |                      |                  |        |

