15. CXCL12 blood sampling at 9:00±2 hours. On Day 2: 24h±2 hours post dose but no later than 11:00. On Day 3 and 14, also plating of blood samples prior to centrifugation for blood culturing, see Section 11.8.1 and Section 11.8.1.2.
16. 48 hours after IMP administration (one biopsy from a CXCL12 treated wound and one from a placebo treated wound)
17. Wound healing assessed by the Investigator (direct observation) and by 3 to 5 independent evaluators using photographs.
18. Wound area assessed by 3 to 5 independent evaluators using photographs and the Image J software (National Institutes of health [NIH]) or equivalent.
19. Baseline wound area measurements based on photos taken after wound punching prior to IMP application.
20. Scar tissue formation assessed by the Investigator (direct observation) and by 3 to 5 independent experts using photographs at Visit 6. Scar tissue formation during the long-term follow-up assessed by the Investigator only. Normal/abnormal and Vancouver scar scale. One assessment per wound.
21. Dressing if indicated.
22. From administration of IMP.
23. Collection of AEs including, but not limited to, mortality, development of any new/recurrent cancer, development of infection, immunogenicity related reactions.
24. For definitions of prior and concomitant medications, see Section 11.3.6.

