14. CXCL12 blood sampling prior to wound punching at 9:00±2 hours, 1 hour post the last wound punch (within 5 minutes of start of IMP application, which should start 1 hour (+/-10% post the last wound punch) and 1 hour (±10%) after the last IMP application.
15. Pre-treatment. The pre-treatment sample should be taken at 9:00±2 hours.
16. Pre-treatment on Day 5, 8, 15 and 19. The pre-treatment samples should be taken at 9:00±2 hours.
17. On Day 3, 5, 8, 15 and 21, also plating of blood samples prior to centrifugation for culturing, see Section 11.8.1 and Section 11.8.1.2.
18. The CXCL12 blood sample should be taken at 9:00±2 hours.
19. Pre-dose Day 1 and pre-dose on Day 19, see Section 11.8.1.
20. Wound healing assessed by the Investigator (direct observation) and by 3 to 5 independent experts using photographs. No assessment by independent experts on Day 17.
21. Wound area assessed by 3 to 5 independent experts using photographs and the Image J software (NIH) or equivalent.
22. Baseline wound area measurements based on photos taken after wound punching prior to IMP application.
23. Scar tissue formation assessed by the Investigator (direct observation) and by 3 to 5 independent experts using photographs Visit 9 to Visit 12. Scar tissue formation during the long-term follow-up assessed by the Investigator only. Normal/abnormal and Vancouver scar scale. One assessment per wound.
24. Day 5, Visit 5.
25. Day 15, Visit 9.
26. At any time between Day 15 and Day 21.
27. Just prior to treatment on Day 2, Day 8 and Day 15.
28. Dressing if indicated.
29. Dressing collection on Day 2 (applied Day 1), Day 3 (applied Day 2).
30. From administration of IMP.
31. Collection of AEs including, but not limited to, mortality, development of any new/recurrent cancer, development of infection, immunogenicity related reaction.
32. For definitions of prior and concomitant medications, see Section 11.3.6.

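### The independent evaluators' Vancouver Scar Scale total cannot be produced as written: no SAD rating and one MAD rating fall in the endpoint window, and photographs cannot show every item

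*Protocol*

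**What the plan says.** **Scar scale.** Section 7.2.1 lists "Vancouver Scar Scale total score on Day 21 and onwards" for SAD and MAD. It names two sources: the Investigator by direct observation and independent evaluators by photography. On the scale itself, Section 11.8.5.1 states: "The scale scores the scar on four parameters: pigmentation, vascularity, pliability and height". It adds: "Each scar will be evaluated by the Investigator and by independent evaluators as detailed in Table 11.8-1". That table grades pliability 0 to 4 (from normal through supple, yielding and firm to adherent), height 0 to 4 in millimetre bands, vascularity 0 to 3 and pigmentation 0 to 3. No version adapted to photographs is given.

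The footnotes to the schedules fix who rates when. In Table 8.1-1 (SAD), footnote 20 has the experts rate photographs "at Visit 6. Scar tissue formation during the long-term follow-up assessed by the Investigator only". In Table 8.1-2 (MAD), footnote 23 has the rating done by the Investigator and "by 3 to 5 independent experts using photographs Visit 9 to Visit 12", and by the Investigator alone in long-term follow-up.

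**Rupture.** Section 7.2.1 also lists the frequency of wound ruptures for both parts. Section 11.8.3 says: "At each post-wound healing visit, it should be documented if the wound is still healed or if any rupture(s) has occurred". The "Wound healing" row ends at Visit 6 (Day 14) in Table 8.1-1 and at Visit 13 (Day 32) in Table 8.1-2. Neither table has a rupture row.

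**The concern.** An endpoint with two named sources needs ratings from both inside its own time window, on items that each source can observe. For the independent evaluators both conditions fail. In the SAD part their contribution would be empty. In the MAD part it would rest on one visit, and the total would contain at least one item that the evaluators would have to guess, leave blank or set to zero by default. A total built that way is not comparable with the Investigator's, and a difference between the two sources would reflect how they look as much as what is there. An analysis plan cannot create ratings that were never scheduled, nor recover a tactile item from an image.

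The rupture point is smaller. If the site follows the table rows alone, rupture is sought for a short time after healing, especially in the SAD part. A count of zero might then partly reflect the schedule.

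**Working it through.** No sample size, power or error rate is involved, and the plan states no figure to reproduce. The check sets scheduled visits against the endpoint definition and sums the scale items.

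**1. Independent scar ratings inside the window (Day 21 and later)**

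| Part | Visits rated by independent experts | Study days | In window |
|---|---|---|---|
| SAD | 6 | 14 ± 1 | 0 of 1 |
| MAD | 9, 10, 11, 12 | 15, 17, 19, 21 | 1 of 4 |

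The MAD visit that qualifies has a tolerance of ± 1 day, so a subject seen on Day 20 also falls outside. MAD Visit 13 (Day 32) carries a scar mark and a photograph, but lies beyond the experts' stated range.

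**2. Items a photograph can support (Table 11.8-1)**

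- Maximum total = 4 (pliability) + 4 (height) + 3 (vascularity) + 3 (pigmentation) = 14.
- Pliability alone: 4/14 = 29%.
- Pliability plus height: 8/14 = 57%.
- Left for a photograph: 3 + 3 = 6 points.

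Pliability is felt, not seen. Height is less clear-cut: Section 11.5 puts a ruler in each photograph, but that gives scale across the skin and not above it. The 3D camera in Section 11.9.1 is a separate exploratory assessment and is not the evaluators' source.

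**3. Photographs already taken inside the window**

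Both tables schedule photographs at 6 weeks and 3, 6 and 12 months (SAD Visits 7 to 10; MAD Visits 14 to 17). MAD Visit 12 is also photographed.

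**4. Rating workload per evaluator**

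Inputs: 12 SAD subjects with 2 wounds left after the Day 3 biopsies, and 24 MAD subjects with 8 wounds. Full attendance is assumed.

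- Now: 12 × 2 × 1 + 24 × 8 × 4 = 24 + 768 = 792 wound ratings.
- Added by rating all four follow-up visits: 12 × 2 × 4 + 24 × 8 × 4 = 96 + 768 = 864 (864/792 = 109% more).
- Added by rating a subset of two visits, for example 6 weeks and 12 months: 12 × 2 × 2 + 24 × 8 × 2 = 48 + 384 = 432 (55% more).

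**5. Tabulated healing checks left after a wound is first recorded as healed (Investigator)**

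- SAD: healed at Day 3, 2 checks left; Day 7, 1; Day 14, 0.
- MAD: healed at Day 5, 8 left; Day 8, 7; Day 10, 6; Day 12, 5; Day 15, 4; Day 17, 3; Day 19, 2; Day 21, 1; Day 32, 0.

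Each part then has 8 long-term visits (SAD Visits 7 to 14, MAD Visits 14 to 21). The Section 11.8.3 rule can apply to these, but they carry no mark in the healing row.

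**The case against.** A reader might infer that the whole Vancouver endpoint fails. It does not. The Investigator scores every scar directly at SAD Visits 7 to 14, and in the MAD part at Day 21 and at every long-term visit, so that total is complete in both parts.

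A reader might also infer that the blinded half of the endpoint is lost. Sections 9.10 and 16.7 keep both the clinical evaluating staff and the independent evaluators blinded. What is lost is a second, independent source. That still has some value, because the Principal Investigator votes on the safety review committee, whose voting members may be unblinded to individual wounds when a stopping rule is triggered.

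Two further points soften the concern without removing it. The synopsis gives the endpoint without the Day 21 limit, so on that wording the Day 14 SAD rating would count; but the synopsis then disagrees with Section 7.2.1, and pliability stays unscorable on either wording. Section 17.6.5 tabulates each item separately, so the evaluators' vascularity and pigmentation scores would remain usable; the named endpoint, however, is the total.

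On rupture, the tempting reading is that in the SAD part it can be detected only if a wound heals by Day 7 and reopens by Day 14. The protocol does not support this. The rule in Section 11.8.3 has no end date and can be read to cover long-term visits. At each of those the Investigator examines the skin of the arms, local tolerability and the scars, and adverse events are collected. The MAD part also allows up to eight tabulated checks after first healing.

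**Conclusion.** The point holds for the independent evaluators' component of the Vancouver total. As written it is empty in the SAD part (0 of 1 rating visit in the window), and in the MAD part it rests on one of four rating visits with a total that is not validly scorable. The visit counts follow directly from the protocol. That pliability cannot be photographed is a measurement judgement from the item labels, and a firm one; for height the judgement is less certain. Pliability alone (29% of the scale) is enough to invalidate the photograph-based total.

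The Investigator's total is unaffected. This is therefore a defect in one component of a descriptive secondary endpoint, worth correcting because the images needed are already scheduled.

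The rupture matter is a mismatch between text and schedule, most limiting in the SAD part, where a wound first recorded as healed on Day 14 has no tabulated recheck. It does not make the rupture endpoint undeliverable.

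**What to change.** 1. In Sections 7.2.1 and 11.8.5.1 and the synopsis, take the Vancouver total from the Investigator only.
2. Make the independent evaluators' vascularity plus pigmentation score (0 to 6) a separate endpoint. Rate it on photographs from SAD Visits 7 to 10 and from MAD Visits 12 and 14 to 17, or from a stated subset. Amend footnotes 20 and 23 to match.
3. Keep the evaluators' overall normal/abnormal scar ratings at SAD Visit 6 and MAD Visits 9 to 12. They feed a different secondary endpoint with no Day 21 limit.
4. State the window by visit for each part, since the SAD part has no Day 21 visit.
5. Complete the ratings of the 12-month photographs before allocation is disclosed to the evaluators under Section 9.10.
6. For rupture, add an Investigator item per wound (healed, still healed, ruptured) at the follow-up visits where the wound sites are already examined, or state the last visit to which the rule applies.

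**Cost.** Wording changes, one added eCRF item, and up to 864 further wound ratings per evaluator (432 for a two-visit subset), each on two items instead of four. No new visits or photographs are needed. The independent data will not cover pliability or height.

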**Table 11.8-1 Vancouver Scar Scale**

| Pliability (P) | Height (H) | Vascularity (V) | Pigmentation (M)  |
|----------------|------------|-----------------|-------------------|
| 0: normal      | 0: normal  | 0: normal       | 0: normal         |
| 1: supple      | 1: 1~2 mm  | 1: pink         | 1: hypopigmented  |
| 2: yielding    | 2: 3~4 mm  | 2: red          | 2: mixed          |
| 3: firm        | 3: 5~6 mm  | 3: purple       | 3: hyperpigmented |
| 4: adherent    | 4: > 6 mm  |                 |                   |

#### 11.8.6 *Assessment of L. reuteri colonies on the skin surrounding the wounds*

At visits specified in Table 8.1-1 and Table 8.1-2, swab samples will be taken from the skin surrounding each wound using sterile swabs (MW176PF Transwab, 40 Compliant). The swab will be taken approximately 1 cm from the wound edge, **before** wound examination and cleaning of the skin.

The swab will be placed back into the sterile container, covered with 30 % sterile glycerol, 2 mL, and stored at -70°C until shipped to [REDACTED] on dry ice.

The samples will be analyzed by [REDACTED] for viable *L. reuteri* R2LC containing the pSIP411 plasmid using a method of culturing conditions specific to detect *L. reuteri* R2LC; PCR and sequencing.

The data will be delivered in an external file.

#### 11.8.7 *Assessment of presence of L. reuteri in feces*

Feces samples will be collected using a feces kit before the first treatment and at visits specified in Table 8.1-1 and Table 8.1-2. A separate fecal sampling instruction manual will be provided to the subjects.

The samples will be shipped to [REDACTED] and analyzed for viable *L. reuteri* R2LC containing the pSIP411 plasmid using a method of culturing conditions specific to detect *L. reuteri* R2LC, PCR and sequencing.

The data will be delivered in an external file.

## **11.9 Assessments related to exploratory endpoints**

### **11.9.1 3D Imaging**

Each wound will be analyzed using a 3D Camera (Cherry Imaging). The wound/scar margin will be outlined using the Image J software (NIH) or equivalent and subsequently analyzed using the Trace software (Cherry Imaging).

Prior to scanning, an assessment of skin type will be performed, which will be documented in the eCRF.

During the scanning process, many small images are acquired. Together the images are merged by the algorithm into a high-resolution stitched 3D model. The models generated by the software are aligned, which enables measurements. The following parameters will subsequently be measured: wound volume, wound area, wound skin pigmentation, scar volume, scar area, scar skin pigmentation and evenness/roughness of the scar.

The data will be delivered in an external file.

### **11.9.2 Microcirculation**

To understand more subtle tolerability affects as well as the impact of the activated ILP100-DP on the immediate skin, microcirculation in the wounds and adjacent skin will be recorded using Laser Speckle Contrast Analysis (LASCA) where blood flow is recorded in an area of 5x10 cm around 2 wound at a time during at least 2 minutes. During this time the subject have to hold the arm still. Data will be recorded at visits specified in Table 8.1-2.

The data will be delivered as an external file. The outcome of the analysis may not be reported in the CSR.

### **11.9.3 Dressing collection for microbiome analysis**

The adhesive, transparent film will be removed from the wound and transferred to and Eppendorf tube or similar. The tube will be placed on dry ice until transferred to a -70°C freezer. Samples will be analyzed for microflora using Illumina or equivalent by an independent contractor.

Dressings will be collected at visits specified in Table 8.1-2 and will be snap frozen and saved at -70°C for future, exploratory microbiome analyses. The analyses are not included in this study.

The outcome of the analysis may not be reported in the CSR.

## **11.10 Appropriateness of measurements**

The stopping rules for dose escalation used (see Section 8.4.1) follows the recommendations and grading system of CTCAE v5.0 but also take into account the recommendations

published by Sibille *et al.*, 2010 which is an adaptation to FIH studies of the grading systems previously proposed by NCI, WHO, NIH and FDA.

All other methods used for safety assessments are commonly used in standard medical care and in Phase I clinical studies.

